### Data Collection and Analysis

#### Clinical Assessment

Evaluators (ie, medical doctor, physical therapist, and neuropsychologist), at the beginning and at the end of the study, conducted the following clinical evaluation scales and tests:

The Movement Disorder Society-Unified Parkinson Disease Rating Scale (MDS-UPDRS) [18] will be used to objectively quantify the motor and nonmotor aspects of PD. Changes in the MDS-UPDRS score will be investigated, with higher scores meaning worse outcomeThe Clinical Dementia Rating Scale (CDRS) [19] will be used to assess the cognitive status of AD and OD. It yields a single score on a scale of 0-5, with higher scores indicating worse outcome. Change in the CDRS score will be measured at baseline and at the end of the studyThe FES-I will be used to evaluate the subjective fear of falling of the patients. It yields a single score on a scale of 16-64, with higher scores indicating worse outcomeThe Pittsburgh Sleep Quality Index (PSQI) [20] will be used to evaluate the quality of sleep. Change in the PSQI score will be measured at baseline and at the end of the study. It yields a single score on a scale of 0-21, where higher scores mean worse outcomeThe State-Trait-Anxiety-Inventory (STAI) [21] will be used to assess the anxiety status (trait and state). Change in the STAI score will be measured at baseline and at the end of the study. It yields a single score on a scale of 20-80, where higher scores mean worse outcomePresence of festination, dysphasia, wandering episodes, and nonprogrammed medical resources use in the last month will be assessed (eg, access to emergency room)The Barthel Index (BI) is an ordinal scale used to measure performance in activities of daily living (ADLs) [22]. Each performance item is rated with a given number of points assigned to each level or ranking. It uses 10 variables describing ADL and mobility and yields a single score on a scale of 0-100, where higher scores mean better outcomeThe PACIC will be used to determine the involvement of the patient in his/her care plan. Change in the PACIC score will be measured at baseline and at the end of the study. It yields a single score on a scale of 0-5, where higher scores mean better outcomeSimilarly, the SAPS was used to evaluate the user’s satisfaction with respect to the medical treatment received. Change in the SAPS score will be measured at baseline and at the end of the study. It yields a single score on a scale of 0-28, where higher scores mean better outcomeThe Cumulative Illness Rating Scale-Geriatric (CIRS-G) [23] is used to include the presence of comorbidities in the clinical profile. Change in the CIRS-G score will be measured at baseline and at the end of the study. It yields a single score on a scale of 0-56, where higher scores mean worse outcome

In addition, patients’ characterization in terms of demographic and clinical data (age, gender, level of education, professional activity, social support, and previous use of technology) was performed.

Demographic and clinical data were aggregated, extracted, and analyzed using dedicated spreadsheet files (Microsoft Corporation).

#### Quality of Life Assessment

The primary outcome of the study will be the difference in quality of life between groups, measured by the EQ-5D-3L scale [24], before and after the experimentation.

The EQ-5D-3L descriptive system comprises 5 dimensions, namely, mobility, self-care, usual activities, pain/discomfort, and anxiety/depression. Each domain was scored by patients through 3 levels: no problems (1), some problems (2), and extreme problems (3) in the execution of the specific item.

Quality of life data were analyzed using dedicated spreadsheet files.

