### Aims

This study represents the third, and last, phase (pilot 3) of large-scale pilots aiming to gradually co-design and iteratively test the PC4L integrated platform and modules.

While pilot phases 1 and 2 focused on technical feasibility and patients’ satisfaction, this protocol focuses on the following objectives:

To assess the impact of using the PC4L platform on patients’ quality of lifeTo compare the metrics generated by the PC4L platform in real-life conditions with the clinical outcome measuresTo evaluate the feasibility and safety of measuring disease progression and patient health status through the global functioning of the PC4L systemTo assess and compare the feasibility and usability of 2 different versions of the PC4L system (fully equipped version vs cloud-based solution)To increase patients’ safety and empowerment

As the primary outcome, the study will provide:

The difference in quality of life between groups (experimental vs control group), measured by the EQ-5D-3L scale at the end of the study

The following secondary outcomes will also be acquired:

The correlation coefficient of the PC4L platform metrics (eg, steps and physical activity levels, sleep, number of falls, cognitive scores) with the clinical outcome measures (eg, motor clinical evaluation, sleep questionnaire, Falls Efficacy Scale-International [FES-I], cognitive evaluations) measured at baseline, end of the study, and the values of change from baselineSystem usability assessment, measured through the System Usability Scale (SUS), at the end of the studyUsers’ satisfaction with the PC4L system, measured through a 5-point Likert Scale, the mHealth User Satisfaction Questionnaire, and the participants’ answers to open questions, at the end of the studyChanges in patients’ satisfaction and empowerment, measured by the Patient Assessment of Chronic Illness Care (PACIC) and the Short Assessment of Patient Satisfaction (SAPS) scales, respectively, at baseline and at the end of the studyChange in patients’ use of medical resources (number of admissions and number of days spent in health institutions) in the last month, measured at baseline and at the end of the study

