### Study Assessments

In-person assessments took place at baseline and at the end of the study (3 months follow-up or at discharge from the rehabilitation program).

Specifically, the sample characterization and clinical evaluation of the participants (both experimental and control group patients) were performed at baseline. The clinical evaluation with specific tests and scales was repeated at the end of the study.

At the beginning and at the end of the study, all patients were assessed on quality of life through a specific scale (EQ-5D-3L).

Only for patients assigned to the intervention group, their experience with the PC4L platform was assessed in terms of usability at the end of the experimental period.

Figure 3 and the “Data Collection and Analysis” section report specific outcomes that will be used.

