### Sample Size

According to published evidence [27], the minimal clinically important difference using the EQ-5D-3L in patients with PD is 5.23 points. The sample size calculation was based on these values and on the data provided in a previous study [28] in the PD field that compared the quality of life of 2 groups of patients, resulting in 10% of difference between groups, corresponding to 6 points. It was estimated that 558 patients, 279 per study group, are necessary to improve 10% in the EQ-5D-3L score, with 95% power. Dropouts were not considered in the calculation. Based on this result, the number of participants was distributed among clinical centers, according to their recruitment capacity (Table 2).

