### Statistical Analysis

Descriptive analysis will be performed for all variables to characterize the sample. For continuous variables, mean, SD, median, and range values will be calculated. For categorical variables, absolute and relative frequencies will be used to describe the data [29-31].

Normality will be studied using the Kolmogorov-Smirnov and Shapiro-Wilk tests. The effect of using the PC4L system will be analyzed by applying the paired-sample *t* test (2-tailed) and the Wilcoxon signed rank test to each variable (statistical significance will be set at P<.05).

The Pearson and Spearman correlation tests will be used to validate the PC4L systems metrics (statistical significance will be set at P<.05).

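### The primary EQ-5D-3L outcome is a between-group difference at the end of the study in one section and a between-group difference before and after in another, and no section says which contrast governs

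*Protocol article*

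**What the plan says.** The protocol article words the primary outcome twice.

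- Aims: "The difference in quality of life between groups (experimental vs control group), measured by the EQ-5D-3L scale at the end of the study". This is one time point, compared between arms.
- Quality of Life Assessment: the outcome is again a difference between the two arms, here "measured by the EQ-5D-3L scale [24], before and after the experimentation". Two time points are named.

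Three other sections bear on which is meant.

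- Study Assessments: "At the beginning and at the end of the study, all patients were assessed on quality of life through a specific scale (EQ-5D-3L". Baseline and final scores are therefore planned for both arms.
- Sample Size: a 10% difference between groups, put at 6 points, is taken from a previous study, and a minimal clinically important difference of 5.23 points is cited. The section then says that 558 patients, "279 per study group, are necessary to improve 10% in the EQ-5D-3L score, with 95% power". It gives no SD, so a reader cannot tell whether the final score or the change was sized.
- Statistical Analysis: "The effect of using the PC4L system will be analyzed by applying the paired-sample". That sentence names a two-tailed paired t test together with its signed-rank counterpart, each judged at P<.05. No between-group contrast is named there.

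**The concern.** The difference in final scores and the difference in change are two test statistics with different standard errors. Their point estimates coincide only if the arms have the same baseline mean. Even then their standard errors differ unless the baseline-to-end correlation is 0.5. In a borderline result, one can cross P<.05 while the other does not.

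The primary outcome is core protocol content that the article states itself, so this is not a detail left to an analysis plan. If it can be read two ways, the trial's conclusion may depend on which section the analyst follows, and a choice made after seeing the data would spend more than the stated 5% error.

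**Working it through.** **Reading the sections together.** Where the article means change, it usually says so and names both visits. The Aims do this for patient satisfaction, empowerment and use of medical resources. Clinical Assessment does it for CDRS, PSQI, STAI, PACIC, SAPS and CIRS-G. The primary outcome in the Aims names only the end of the study. By that pattern, the wording in Quality of Life Assessment leans towards change. A signed-rank or paired t test compares a patient with himself or herself, so as written it computes neither between-group contrast.

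**Inputs from the article.** n = 279 per arm, 1:1 allocation, 95% power, P<.05 with a two-tailed t test, effect 6 points, minimal important difference 5.23 points, dropout not considered.

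**Assumptions.** The article gives neither an SD nor a baseline-to-end correlation r. I solve for the SD that makes 279 per arm give 95% power at 6 points and assign it to the scores at both visits. I let r run from 0.3 to 0.8 and use a normal approximation.

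**1. Implied SD.**
SD = 6 × √(279/2) / (1.960 + 1.645) = 6 × 11.81 / 3.605 = 19.66.
Without a stated SD, the 558 can be neither confirmed nor refuted. If 5.23 points had been the target, the implied SD would be 17.14.

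**2. Standard errors.**
- End of study: 19.66 × √(2/279) = 1.664.
- Change: 1.664 × √(2(1 − r)).
- Baseline-adjusted (ANCOVA): 1.664 × √(1 − r²).

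**3. Power at 6 points**, as Φ(6/SE − 1.960). For example, for change at r = 0.3, SE = 1.664 × √1.4 = 1.969, and Φ(3.047 − 1.960) = 86.1%.

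| r | SD of change | End of study | Change | ANCOVA |
|---|---|---|---|---|
| 0.3 | 23.26 | 95.0% | 86.1% | 96.6% |
| 0.5 | 19.66 | 95.0% | 95.0% | 98.6% |
| 0.7 | 15.23 | 95.0% | 99.6% | 99.9% |
| 0.8 | 12.43 | 95.0% | about 100% | about 100% |

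The 95.0% column is true by construction, because the SD was solved to give it.

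**4. Disagreement and type I error.** The two z statistics are jointly normal with correlation √((1 − r)/2). The bivariate normal distribution then gives:

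| r | Exactly one significant, 6 points | Exactly one significant, 5.23 points | No effect: at least one significant |
|---|---|---|---|
| 0.3 | 13.2% | 21.1% | 8.8% |
| 0.5 | 7.6% | 15.5% | 9.1% |
| 0.7 | 5.1% | 12.2% | 9.4% |
| 0.8 | 5.0% | 11.9% | 9.5% |

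**The case against.** The case for leaving this alone is substantial, and much of it stands.

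- **It may be only a wording difference.** Both sections name the same instrument and both say between groups. The second could simply list the visit times, as Study Assessments does. That reading is possible, so this is an unresolved ambiguity and not a flat contradiction. A reader might infer that the second definition is a within-group before-and-after comparison; its own words exclude that.
- **The target is the same.** Under 1:1 randomisation both contrasts have the same expected value. They part through chance baseline imbalance and precision, not because they measure different effects.
- **No error inflation is written into the plan.** A reader might conclude that the trial's type I error is nearly doubled. Nothing in the article permits a claim on whichever contrast succeeds, so the 9% is conditional on the choice staying open.
- **Change scores need not lose power.** The loss appears only for r below 0.5; above that, change gains.
- **The sample size is not clearly built on two bases.** One could read "are necessary to improve 10% in the EQ-5D-3L score, with 95% power" as within-patient improvement. It directly follows the 10% difference between groups and most naturally repeats it.
- **ANCOVA is partly a preference.** Both unadjusted contrasts are valid in a randomised trial, and covariate adjustment is often left to an analysis plan.

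What survives is that the article words its primary outcome in two ways, that the more natural readings differ, and that the sections which could break the tie do not.

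**Conclusion.** The concern holds as an ambiguity in the primary contrast. It does not show that the trial is under-powered, that its error rate is inflated as planned, or that the two definitions pursue different effects.

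Its size is moderate at the planned effect: the two contrasts give different significance verdicts in about 1 trial in 20 to 1 in 8 at 6 points, and in about 1 in 8 to 1 in 5 at 5.23 points. Power for the change contrast at 6 points could be anywhere from 86% to about 100%, against 95% for the end-of-study contrast. All of this rests on the back-solved SD of 19.66, no dropout and an assumed correlation of 0.3 to 0.8, none of which can be checked against a figure in the article except that dropout was left out of the calculation.

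The point is worth acting on because the primary contrast decides the trial's conclusion and settling it costs almost nothing.

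**What to change.** - In Aims, Quality of Life Assessment and Statistical Analysis, state one primary contrast in the same words: the between-group difference in end-of-study EQ-5D-3L score, adjusted for baseline EQ-5D-3L by ANCOVA, two-sided alpha 0.05. Under the assumptions above its power is at least that of either unadjusted contrast at every correlation tried.
- Label the unadjusted end-of-study difference and the difference in change as sensitivity analyses that carry no claim.
- In Sample Size, say that the 10% (6 points) is the between-group difference, and give the SD used and whether it belongs to the final score or to change.
- Settle this before comparative data are examined. Enrollment ended in February 2023, results were expected in summer 2023 and the article is dated 24 July 2023, so that window may have closed. If it has, report the choice as a dated change and show all three contrasts.

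The cost is a sentence or so in each section and a little more analysis work. Baseline EQ-5D-3L is already collected in all patients, so no new data are needed.

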#### Usability and Satisfaction Assessment

At the end of the experimental period, patients allocated to the experimental group performed the usability evaluation of the PC4L platform solution by means of the SUS [17], Global Satisfaction and mHealth User Satisfaction questionnaires, adverse events reporting, and end-of-study open questions.

The SUS is used to measure how easy or difficult the proposed system is to use. We will compare the usability of 2 different versions of the PC4L system (fully equipped and cloud-based solutions). The overall SUS score will be calculated and assessed consistently with the literature: a score of 100 corresponds to the best imaginable usability, while acceptable usability is defined by an SUS score above 68 points [17,25].

The Global Satisfaction Questionnaire is used to assess the overall level of satisfaction or dissatisfaction with the platform experience.

The mHealth User Satisfaction questionnaire is used to measure user satisfaction and usability of the recommendation component of the solution [26].

As a completion of end-of-study assessment, an adverse events report and end-of-study open questions of preferred and less preferred aspects of the platform, as well as suggestions for improvements, will be collected for each user.

### Sample Size

According to published evidence [27], the minimal clinically important difference using the EQ-5D-3L in patients with PD is 5.23 points. The sample size calculation was based on these values and on the data provided in a previous study [28] in the PD field that compared the quality of life of 2 groups of patients, resulting in 10% of difference between groups, corresponding to 6 points. It was estimated that 558 patients, 279 per study group, are necessary to improve 10% in the EQ-5D-3L score, with 95% power. Dropouts were not considered in the calculation. Based on this result, the number of participants was distributed among clinical centers, according to their recruitment capacity (Table 2).

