**Results:**

The study protocol is part of a project approved and funded by the European Commission Horizon 2020 (grant agreement number 875221). The ethics committees of all involved centers reviewed and approved the study protocol. The study began with the recruitment phase in September 2022, and enrollment ended in February 2023. Recruitment is now closed (April 2023). The results of this study are expected to be published in summer 2023. A total of 558 patients, 279 per study group, were recruited. The results will allow to clarify the impact of PC4L on quality of life, will assess the empowerment of patients and the medical resources use, as well as the usability of the final version of the PC4L system. It will also provide information on the support of the system as a tool to facilitate the decision-making process.

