### Recruitment

Patients with PD and other parkinsonian syndromes, AD, or ODs were invited to participate from the clinical centers involved in the study. Each participant organization was assigned to recruit a number of participants related to their skills, experience, number of researchers involved, and access to users (Table 2).

**Table 2 table2:** Distribution of participants per clinical center and scenario.

Scenario/clinical center	Rehabilitation (n=204), n	Day care (n=82), n	Home (n=272), n	Total (N=558), n
APM^a^	80	N/A^b^	26	106
CCP^c^	63	N/A	62	125
CNS^d^	46	N/A	86	132
UHB^e^	15	N/A	15	30
UMF^f^	N/A	30	30	60
WBW^g^	N/A	52	53	105

^a^APM: Asociacion Parkinson Madrid.

^b^N/A: not applicable.

^c^CCP: Casa di Cura del Policlinico.

^d^CNS: Campus Neurológico Sénior.

^e^UHB: University and Emergency Hospital of Bucharest.

^f^UMF: University of Medicine and Pharmacy.

^g^WBW: Wohlfahrtswerk für Baden-Württemberg.

To reach the planned number of recruits, many strategies were implemented: participants were contacted through online webinars; through brochures placed in specific centers such as pharmacies, leisure centers, and medical offices; and through patients’ associations. Further, regular updates were posted via online newsletters on different websites, such as the PC4L website and end users organizations’ websites. In addition, information about the PC4L pilot 3 study was shared during national and international conferences. Recruitment was also promoted in a collaborative way thanks to partners from other European projects. Finally, participants were recruited in person when accessing the medical facilities and via phone contact or emails after searching local databases.

Patients who discontinue the study participation because of medical conditions (ie, infections, falls, medical emergencies) or unwilling to participate any longer for other reasons (ie, difficulty with technology, loss of interest) will be considered dropouts.

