### Randomization

Patients were randomized in a ratio of 1:1 to the intervention group (use the PC4L system) or the control group (no intervention) by an independent, nonclinical partner of the project consortium.

Patients allocated in the intervention group were randomized in a ratio of 3:1 to the “cloud-based solution” and the “fully equipped” PC4L system version.

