### Withdrawal of Participants

Participation in this study is voluntary. Patients may withdraw from the study at any time, without giving reasons and without disadvantage in terms of the quality of care they would receive if they did not participate. After the withdrawal, no further data will be collected or taken into consideration for statistical purposes.

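### The 95% power claim for 558 patients holds only with complete follow-up: no dropout allowance was made, and exactly 558 were recruited

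*Protocol article*

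**What the plan says.** All references are to the protocol article.

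- **Sample Size** sets the number and the claim: "It was estimated that 558 patients, 279 per study group, are necessary to improve 10% in the EQ-5D-3L score, with 95% power". The effect comes from an earlier two-group study in Parkinson disease, "resulting in 10% of difference between groups, corresponding to 6 points". The same paragraph cites a threshold: "the minimal clinically important difference using the EQ-5D-3L in patients with PD is 5.23 points". It closes with "Dropouts were not considered in the calculation". It gives no SD, alpha, sidedness or scoring scale.
- **Abstract, Results** reports the outcome of recruitment: "A total of 558 patients, 279 per study group, were recruited". Table 2 distributes the same 558 over the centers.
- **Recruitment** defines dropouts. They include patients who stop for medical reasons and those "unwilling to participate any longer for other reasons (ie, difficulty with technology, loss of interest) will be considered dropouts". No rate is given.
- **Withdrawal of Participants** says that after withdrawal "no further data will be collected or taken into consideration for statistical purposes".
- **Study Assessments** says EQ-5D-3L is measured in all patients at the start and at the end.

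**The concern.** A calculation without a dropout allowance yields the number of patients who must supply the primary outcome. Here that number and the number recruited are the same. The article names reasons why patients may leave and collects nothing afterwards, so each loss takes the evaluable number below the one on which the 95% rests. The article states that dropouts were ignored, but not what power remains, and without an SD a reader cannot check it directly.

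The Discussion defends the randomized design partly on the ground that the sample is large enough for power. If the trial shows no difference, readers will weigh that result against a 1-in-20 chance of missing the planned effect. With losses the chance is higher, for example about 1 in 10 at an assumed 20% loss.

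**Working it through.** **Inputs from the article.** 279 per group, 6 points, 95% power (Sample Size); 1:1 allocation (Randomization); significance at .05 and a two-tailed test (Statistical Analysis, where they are attached to the analysis and not to the sample size).

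**Assumptions.** Two-sample comparison of means; two-sided 5%; 6 points as the planning effect; equal proportional loss in both groups; loss rates of 5%, 10%, 20% and 30%, none of which stands in the article.

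**Step 1. The plan's own figure.** Without an SD, 279 cannot be reproduced independently. It can only be inverted:

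SD = 6 × √(279/2) / (1.960 + 1.645) = 6 × 11.811 / 3.605 = 19.66 points, a standardized effect of 6/19.66 = 0.305.

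The noncentral t gives 19.62. By construction, 279 per group then has 95.0% power.

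**Step 2. Power after loss.** With n = 279 × (1 − loss), SE = 19.66 × √(2/n) and power = Φ(6/SE − 1.960):

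| Assumed loss | n per group | SE | 6/SE | Power |
|---|---|---|---|---|
| 0% | 279 | 1.664 | 3.605 | 95.0% |
| 5% | 265.1 | 1.708 | 3.513 | 94.0% |
| 10% | 251.1 | 1.755 | 3.420 | 92.8% |
| 20% | 223.2 | 1.861 | 3.224 | 89.7% |
| 30% | 195.3 | 1.990 | 3.016 | 85.5% |

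The noncentral t agrees to about 0.1 percentage point.

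**Step 3. How far this depends on the inferred inputs.** The ratio 6/SE equals 3.605 × √(1 − loss). Power at the planning effect therefore does not depend on the SD, nor on whether 6 or 5.23 points was the planning effect. Sidedness matters a little: a one-sided 5% test back-solves to SD 21.54 and gives 94.1%, 93.0%, 90.3% and 86.6% at the four loss rates.

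**Step 4. Context: 5.23 points.** If 6 points was planned, power at 5.23 with no loss is Φ(5.23/1.664 − 1.960) = Φ(1.182) = 88.1%. At an assumed 20% loss it is Φ(5.23/1.861 − 1.960) = Φ(0.850) = 80.2%. If 5.23 was planned instead, the implied SD is 17.14 and power at 5.23 with no loss is 95%.

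**Step 5. Adjusting for baseline.** Adjustment multiplies the SD by √(1 − r²), where r is the correlation between baseline and end-of-study scores. This treats the back-solved SD as that of the end-of-study score. At 20% loss the ratio 3.224 is divided by √(1 − r²):

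| Assumed r | √(1 − r²) | Ratio | Power for 6 points |
|---|---|---|---|
| 0.3 | 0.954 | 3.380 | 92.2% |
| 0.5 | 0.866 | 3.723 | 96.1% |
| 0.7 | 0.714 | 4.515 | 99.5% |

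**The case against.** The strongest reply is that nothing is hidden. The sentence after the power claim says dropouts were left out, so a careful reader knows that 558 presumes complete follow-up. No arithmetic slip has been shown, and none can be without the SD. The cost is also small: about 1 percentage point at 5% loss, 2 at 10%, and still 85% power at 30%. All of this stands and limits the weight of the point. It does not remove it, because the disclosure does not say what power remains.

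Three stronger readings are tempting, and the article does not support them.

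- **That the protocol expects losses of 10% to 30%.** It defines dropouts and gives example reasons, with no rate. The range is an assumption made here.
- **That sizing for 6 points and not 5.23 is an error.** Power is always conditional on a chosen effect, and the article says where its 6 points come from. The 5.23 is cited for Parkinson disease only, whereas the trial also enrolls Alzheimer disease and other dementias. The article says the calculation used both values; the wording about a 10% improvement favors 6 points but does not settle it.
- **That power at 5.23 points is only 75% to 85%.** That range combines the smaller effect with an assumed 10% to 30% loss. The smaller effect alone gives about 88%.

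**Conclusion.** The point holds in limited form. The article claims 95% power from 558 evaluable patients, recruited exactly 558, foresees dropouts and takes no further data after withdrawal. The 95% is therefore the power with zero loss, the most favorable case.

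Power for the 6-point difference is about 94%, 93%, 90% and 85% at an assumed 5%, 10%, 20% and 30% loss. This rests on a two-sided 5% two-sample test; a one-sided reading raises the figures by about 1 point at most. The figures of about 88% (no loss) and 80% (assumed 20% loss) at 5.23 points are context only, and apply only if 6 points was the planning effect.

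This does not show an underpowered trial. It shows a power statement that should be made conditional and checkable.

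**What to change.** 1. **State the inputs**: the SD, alpha, sidedness and EQ-5D-3L scale behind the 6 points. The article describes five items scored 1 to 3. Their sum would run from 5 to 15, which cannot carry an SD near 19.6, so the scale needs naming.
2. **Restate the claim**, for example: with complete follow-up, 558 randomized patients give 95% power for a 6-point difference; under assumed losses of 5%, 10%, 20% and 30%, power is about 94%, 93%, 90% and 85%. Label the rates as assumptions, and replace them with the observed loss when it is known.
3. **Compare the two groups on end-of-study EQ-5D-3L, adjusted for baseline.** Baseline is already measured in both groups. The gain depends on the actual correlation: in the cases worked above it largely or fully offsets a 20% loss. It recovers precision only and does not remove bias if dropout differs between groups.

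The cost is a slightly less favorable power statement and a specified adjusted comparison. Recruitment is closed and no patients need be added.
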